#### Comparison arm

Activities for the comparison arm will consist of prompts to men via cell phone messages to breathe into their breathalyzer once every other evening. Breathalyzer scores and a photo of the participant's face will be immediately recorded and stored in the Soberlink© system. The participation reward will be split into immediate earnings (which participants can come into the office to collect throughout the study) and savings (which will be deposited into their bank accounts as a lump sum at the end of the study). At the conclusion of the intervention period, men enrolled in the comparison arm will participate in a 60–90 min, community-requested alcohol education module focusing on couple's conflict management and economic goals.

#### Incentives arm

Couples enrolled in the incentives arm will participate in all of the activities described above for the comparison arm except that they will receive twice-daily prompts to breathe into their breathalyzer. Given our intention to combat IPV, which generally was posited to occur in the evenings when both partners are home, this pilot study incentivized sobriety in the evenings by scheduling daily breathalyzer tests in the evenings and early mornings. Couples will learn how the incentives are tied to breathalyzer scores and will be walked through a goal-setting exercise in which couples decide on goals they would like to save for such as children's education savings goals, individual savings goals, and business savings goals. Like comparison arm participants, daily and weekly activities for the incentives arm also consist of daily prompts to men to breathe into their breathalyzer via cell phone messages; however, these men will receive larger incentives for negative breathalyzer tests. Men will come in to the study office to receive their participation fees and a proportion of their breathalyzer test rewards, and will allocate another portion of the incentives to the goals they selected during the orientation session. A distinction was made between immediate rewards and long-term rewards for saving in our study design to allow men to feel that they were earning money for their behavior change that they could control, while also addressing a need to ensure the intervention contributed positively to family goals and shared financial decision-making with their female partners.

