## Abstract

**Introduction:** Evidence suggests alcohol consumption is correlated with intimate partner violence (IPV) making alcohol reduction interventions a promising method for reducing IPV. While both financial incentive and cognitive behavioral therapy (CBT) interventions in high-income countries, respectively, have effectively reduced alcohol consumption and IPV perpetration among men, little evidence exists demonstrating that these approaches can work in a low-resource setting.

**Methods:** The objective of this study is to design and pilot test a low-cost, scalable intervention for reducing alcohol consumption and IPV in Bengaluru, India, where alcohol has been shown to be a key driver of high rates of IPV. A pilot randomized controlled trial (RCT) design will be used to examine the feasibility of testing a combined incentive and CBT based intervention among couples to stimulate immediate behavior change and to sustain positive behaviors pertaining to alcohol use and IPV. Sixty couples will be screened and enrolled into one of three study arms: an incentive-only, incentive plus counseling, or a control arm. Extensive procedures have been included to ensure participant safety, including staff training on global safety procedures for violence intervention research, careful messaging of study aims, screening procedures to exclude those at high risk of alcohol withdrawal or severe violence due to the study, and a referral and case management system. Male and female participants will complete surveys at baseline and immediately and 3-months post-intervention. Breathalyzers will be used to capture male participants' blood alcohol content daily for intervention arm participants and three times a week for control participants. A sub-sample of male and female members of couples will participate in qualitative in-depth interviews to further explore pathways to change. The results from this preliminary study will inform the development of a larger RCT study of male alcohol and IPV reduction.

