### Study design

This study is a randomized control pilot study of *Beautiful Home*, an innovative combined incentive-based and BCT intervention developed with input from community partners for the mitigation of male alcohol use and IPV among couples in a slum in Bengaluru, India. Figure 1 depicts our Theory of Change (TOC). We hypothesize that the *Beautiful Home* intervention is feasible and can be delivered safely, leading to improvements in short-term alcohol reduction as a result of financial incentives. When combined with BCT, we posit the intervention will enable couples to learn skills that will support longer-term change related to alcohol use and IPV. Based on the results of this pilot, we will refine our approach, and determine the merit of a future phase 3 trial of the intervention.

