**Figure 1 F1:**
[figure not shown]
*Beautiful Home* intervention Theory of Change (TOC).

The study will be conducted with 60 couples randomized into one of three arms: an incentive-only arm, an incentive-plus-counseling arm, and a comparison arm. The design mimics the proposed design of a follow-on randomized control trial, and allows for testing the feasibility and acceptability of the study design, as well as offering an opportunity to determine whether the combined approach of incentives and counseling performs better than an incentive-only intervention. During the intervention, breathalyzer data will be collected daily for the first 4 weeks from men using Soberlink© breathalyzer technology that allows for photo capture to ensure the appropriate person is taking the test. A period of 4 weeks was chosen for the incentives portion of the intervention based on the duration of Schilbach's study (10) and to preserve the team's flexibility to adapt if the initial incentive structure was not affecting drinking. Participants in the incentive-plus-counseling arm will participate for an additional 2 weeks (6 weeks) to accommodate counseling sessions. No breathalyzer data will be collected for the additional 2 weeks. Women and men will complete a baseline survey, as well as surveys immediately and 3 months post-intervention. A sub-sample of male and female participants from each study arm (~4 couples per arm) will participate in qualitative in-depth interviews to gain feedback about their participation in the intervention, including around processes of change (i.e., what pathways contribute to changes in alcohol and violence reduction) that might inform the content of future interventions. See Figure 2 for a diagram of study flow and data collection points.

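### Incentives versus comparison tests a package of payment, closer breath monitoring and goal setting, so the hypothesised reduction cannot be credited to financial incentives alone

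*Protocol article*

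**What the plan says.** All references are to the protocol article.

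- **Hypothesis (Study design).** The intervention is expected to be feasible and safe, "leading to improvements in short-term alcohol reduction as a result of financial incentives". Counseling is then expected to support longer-term change.
- **Comparison arm.** Men receive "prompts to men via cell phone messages to breathe into their breathalyzer once every other evening". They earn a reward for participating, part paid during the study and part saved. The section does not say whether the reward depends on the reading.
- **Incentives arm.** Activities are those of the comparison arm "except that they will receive twice-daily prompts to breathe into their breathalyzer". Evening sobriety is incentivised by "scheduling daily breathalyzer tests in the evenings and early mornings". Couples also choose savings goals in a guided exercise. Later the same section speaks of daily prompts, likens them to those of the comparison arm, and adds that "these men will receive larger incentives for negative breathalyzer tests".
- **Abstract.** Breath alcohol is captured "daily for intervention arm participants and three times a week for control participants".
- **Study design, after Figure 1.** Without distinguishing arms, "breathalyzer data will be collected daily for the first 4 weeks from men". The same paragraph sets the incentive period at 4 weeks, says the design is built to mirror that of the later trial, and names combined versus incentive-only as a comparison of interest.
- **Incentives and counseling arm.** These couples do everything in the incentives arm and add four counseling sessions.

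**The concern.** An effect can be credited to one component only if the two arms differ in that component alone. Here randomization assigns contingent payment, a denser testing schedule, an extra time of day for testing, and a goal-setting exercise all together. Frequent testing with a photograph of the man's face may itself change drinking, and setting savings goals may do so too. Randomization does not separate these, because all of them are part of the assigned treatment.

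The wording of the payment rule adds a second uncertainty. Saying that incentive men get larger incentives for negative tests invites the question whether comparison men get smaller ones. If they do, the contrast is not incentive against none.

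What is at stake is interpretation. The Expected outcomes section makes evidence of an effect on alcohol use one of the findings that favour a follow-on trial, and the pilot's design is meant to carry over. A statement that payment reduced drinking would then rest on a contrast that cannot show it, and a larger trial of the same form would estimate the same mixture more precisely.

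**Working it through.** The plan states no figure for this point, so there is none to reproduce. The check has four steps: count scheduled tests, list what differs, see what the three arms can identify, and ask whether analysis could repair it.

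**1. Scheduled tests over 4 weeks (28 days; Study design)**

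| Arm | Source | Frequency | Tests |
|---|---|---|---|
| Incentives | Incentives arm | twice daily | 28 × 2 = 56 |
| Incentives | Abstract | daily | 28 × 1 = 28 |
| Comparison | Comparison arm | every other evening | 28 / 2 = 14 |
| Comparison | Abstract | three a week | 4 × 3 = 12 |

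Ratios, incentives to comparison:

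- 56 / 14 = 4.0 (both arm sections)
- 28 / 12 = 2.3 (both from the Abstract)
- 56 / 12 = 4.7 and 28 / 14 = 2.0 (mixed sources)

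The range is 2.0 to 4.7. Only the arm-neutral statement "breathalyzer data will be collected daily for the first 4 weeks from men", if applied to every man, would give equality (28 / 28 = 1). Both the Abstract and the Comparison arm section contradict that reading. The remark in the Incentives arm section that likens its daily prompts to those of the comparison arm conflicts with them in the same way.

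**2. What else differs between incentives and comparison**

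| Feature | Comparison | Incentives |
|---|---|---|
| Time of tests | evening | evening and early morning |
| Savings goal-setting exercise | not listed | yes |
| Payment for negative tests | not stated | yes, described as larger |

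**3. What the arms identify**

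Write P for contingent payment (relative to whatever comparison men receive), M for the extra monitoring, G for goal setting and C for counseling. Ignoring interactions:

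- incentives − comparison = P + M + G
- combined − incentives = C

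Three arms give two independent contrasts for four unknowns. P cannot be solved from the first contrast, because no arm has M without P. M cancels from the second contrast, because both arms follow the incentives-arm schedule.

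**4. Can matched test occasions repair it?**

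Restricting the analysis to evenings tested in both arms equalises measurement. That is worth doing. If each test were independently positive with probability 0.2 (an assumption, not a figure in the article), the weekly chance of at least one positive, 1 − 0.8ⁿ, would be 0.49 with 3 tests, 0.79 with 7 and 0.96 with 14, with no difference in drinking. Matching removes that artefact, but it leaves any effect on behaviour of being tested more often.

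**The case against.** The strongest reply is that testing is how the incentive is delivered. A payment for negative readings needs readings, and goal setting decides where the saved portion goes. Comparing such a package with a lighter-touch control is a legitimate choice. The pilot's objectives are recruitment and retention, breathalyzer use and engagement with counseling; effects are called preliminary, and the Sample size section says the study is not powered. The criteria for a follow-on trial speak of the impact of the intervention, not of payment alone. The article also already names combined versus incentive-only as a comparison of interest.

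Most of this stands. It limits the point to attribution and leaves the feasibility aims untouched. It does not rescue the sentence in Study design that credits incentives. If the package is what is meant, the hypothesis should say so.

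Three stronger readings are tempting and are not supported:

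- **The monitoring ratio is at least 4 to 1.** That takes the twice-daily statement alone. The daily statements bring the ratio down to 2.3 or 2.0.
- **Comparison men are paid for sobriety, so the control is a low-dose incentive arm.** The Comparison arm section mentions only a reward for participating, and the Incentives arm section separates participation fees from test rewards. The word larger may refer loosely to total payment. The text leaves this open. Were it true, it would tend to dilute a difference rather than create a false one.
- **Any observed effect may be due to monitoring alone, so the contrast is worthless.** The share due to monitoring is not identified, which is not evidence that it is large. The package effect can still be estimated.

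**Conclusion.** The point holds as one of attribution. On every arm-specific statement in the article, incentive men are scheduled for more breath tests than comparison men, by a factor of 2.0 to 4.7 over 28 days. They are also tested in the early morning and complete a goal-setting exercise. Incentives versus comparison therefore estimates a package effect, and a payment-only effect cannot be claimed from it. Combined versus incentive-only is not affected by the testing difference.

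This rests on the arm sections and the Abstract describing what will be done, and on the listed activities being complete for each arm. It does not depend on how strongly monitoring changes drinking, which the article gives no means of judging. Whether comparison payment depends on the reading remains unresolved.

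**What to change.** 1. **Restate the claim.** In Study design, and in any conclusion or go-decision drawn from incentives versus comparison, describe the effect as that of the incentive-plus-monitoring package, including goal setting. Do not claim an effect of payment alone. Cost: wording only.
2. **Reconcile test frequency** across the Abstract, the paragraph after Figure 1 in Study design, the Comparison arm section, and the two statements in the Incentives arm section. Cost: wording only.
3. **Reconcile the payment statements** in the Comparison arm and Incentives arm sections, so that it is clear whether comparison-arm payment depends on the reading. If it does, describe the contrast as larger versus smaller incentives. Cost: a sentence.
4. **Optional, for the follow-on trial:** consider one testing schedule for all arms. It would remove the difference in monitoring, at the price of extra prompts and handling for the comparison arm (about 20 men at the pilot's size), and it may itself lower drinking there. This is a trade-off to weigh, not a required change.

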As a result, alcohol reduction interventions are a promising channel for combatting IPV. Several evidence-based individual and couple-level interventions offer potential cost-effective solutions. In particular, there is a large body of evidence supporting the effectiveness of small financial incentives in promoting behavior change in low-resource settings, including India, Mexico, and Tanzania (8–10). In this approach, called contingency management, financial incentives reduce alcohol use by giving drinkers a short-term financial benefit in exchange for abstaining from alcohol use. These financial incentives aim to offset the immediate benefits drinkers might experience from consuming alcohol and make the long-term benefits of avoiding harmful drinking behavior (or conversely the negative consequences of engaging in harmful drinking) salient in the present. Schilbach (10) found that small incentives given to rickshaw drivers in Chennai, India both significantly reduced daytime drinking and increased savings by 60%. In Schilbach's experiment, 229 rickshaw drivers were randomized to one of several conditions involving financial incentives over the course of 3 weeks. Sobriety was measured using a daily breathalyzer test taken at the study office. The study found reduced daytime drinking (i.e., around the time of the breathalyzer tests), however, because drinking at other times increased, overall no reduction in alcohol consumption was observed.

Although small incentives can create short-term behavior change, they do not seem to create long-term change (11). However, when combined with behavioral couples' therapy (BCT) [i.e., couples counseling that uses cognitive behavioral therapy (CBT) as its base] designed to increase sobriety, provide men with alcohol reduction tactics and improve couples' communication (12), an intervention may have more sustained results for reducing IPV and alcohol use. A study in Liberia testing a CBT intervention compared to a CBT and cash-incentive intervention among criminally engaged men found effects were sustained longer among those receiving the combined intervention of cash incentive and CBT (13).

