#### To assess effects on safety and intermediate outcomes

Descriptive statistics will be calculated to describe participants' social and economic characteristics, relationship factors, gender norms and attitudes, and alcohol use risk behaviors. Descriptive statistics will also be calculated separately by intervention arm so that variations in distributions can be examined.

Most measures to be used in the analyses have been reported and validated in earlier studies. For some (e.g., gender norms), items will be grouped into scales conceptually and by examining item correlations through the use of factor analysis and other multidimensional scaling techniques.

We will examine whether there are systematic differences between individuals with missing data and those without. If missing data appear to be informative (e.g., missing systematically), we will employ appropriate ad hoc imputation methods to impute missing values.

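### Breath tests differ by arm in frequency and time of day, and the sections disagree on the schedule, so unmatched breath-test summaries cannot be compared between the incentive arms and the comparison arm

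*Protocol article*

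**What the plan says.** Four places in the protocol article describe the breath-test schedule.

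- **Abstract:** tests are "daily for intervention arm participants and three times a week for control participants".
- **Study design:** "breathalyzer data will be collected daily for the first 4 weeks from men", with no distinction by arm. No breath data are collected in the two extra weeks of the counseling arm.
- **Comparison arm:** "prompts to men via cell phone messages to breathe into their breathalyzer once every other evening".
- **Incentives arm:** "they will receive twice-daily prompts to breathe into their breathalyzer", with the rationale of rewarding evening sobriety by "scheduling daily breathalyzer tests in the evenings and early mornings". A later sentence in the same section likens the incentives arm to the comparison arm and calls the prompts daily in both. It adds that incentive men earn larger incentives for negative tests.

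The Incentives and counseling arm section carries over all activities of the incentives arm, and so its test schedule.

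The Objectives name male partner sobriety among the primary outcomes for preliminary effects, and describe breathalyzers as a measure of sobriety. Expected outcomes and results lists alcohol use reduction, and the direction of alcohol trends, among the findings that would favor a follow-on trial.

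**The concern.** There are two linked problems.

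First, the sections cannot all be true. A reader cannot tell how many tests each man should take, or whether comparison men are tested daily or on alternate days. Without a fixed number of prompts, the share of prompts answered has no defined denominator, although consistent breathalyzer use is itself a feasibility objective.

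Second, on the detailed descriptions by arm, early-morning readings exist only in the rewarded arms, and those arms are prompted up to four times as often. A summary that depends on when or how often men are tested will then differ between arms even if the men drink identically.

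The pilot has about 20 couples per arm and is stated not to be powered for significance. Direction of effect is therefore what will be read, and a measurement artifact that creates a direction could mislead the decision on a larger trial.

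**Working it through.** **1. Scheduled tests per man over 4 weeks (28 days)**

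| Source | Incentive arms | Comparison arm | Ratio |
|---|---|---|---|
| Abstract | 28 × 1 = 28 | 3 × 4 = 12 | 2.33 |
| Study design | 28 | 28 | 1 |
| Incentives arm and Comparison arm sections | 28 × 2 = 56 | 28 / 2 = 14 | 4 |
| Incentives arm, later sentence | 28 (prompts called daily) | 28 | 1 |

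The comparison figures of 12 and 14 are close and may be loose wording for the same thing; 28 is not. The incentive-arm figures differ by a factor of 2, unless daily means on each day rather than once a day.

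**2. Pooled share of positive tests, identical drinking in all arms**

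Let pe be the probability of a positive evening test and pm that of a positive morning test. Both are assumed.

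- Comparison arm, evenings only: share = pe.
- Incentive arms, evening plus morning: share = (pe + pm)/2.
- Artificial benefit: (pe − pm)/2.

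With pe = 0.50 and pm = 0.10, the shares are 0.50 and 0.30, a gap of 20 points. With pm = 0.20 they are 0.50 and 0.35, a gap of 15 points. Over pe from 0.30 to 0.70 and pm from 0.02 to 0.15, the gap runs from (0.30 − 0.15)/2 = 7.5 points to (0.70 − 0.02)/2 = 34 points. It is zero if there is no morning test, or if mornings are as often positive as evenings.

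**3. Any positive test during the period**

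With probability p per evening, and evenings taken as independent, the chance of at least one positive is 1 − (1 − p)^n. At p = 0.05 this is 0.51 for n = 14 and 0.76 for n = 28. The arm tested more often now looks worse by about 25 points, before morning tests are added.

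**4. Common evenings only**

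If every arm is compared on the same evenings (14 per man, or 12 at three a week), the expected share is pe in each arm. The schedule artifact is then zero.

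**5. Missed tests, evenings only, pe = 0.50 (assumed)**

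Suppose a fraction s of positive tests is skipped in the incentive arms alone, and missed tests are left out. The observed share is pe(1 − s)/[pe(1 − s) + (1 − pe)].

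| s | Observed share | Artificial benefit |
|---|---|---|
| 10% | 0.45/0.95 = 0.474 | 2.6 points |
| 30% | 0.35/0.85 = 0.412 | 8.8 points |
| 50% | 0.25/0.75 = 0.333 | 16.7 points |

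Now suppose a fraction m is missed at random and counted as not sober. The share is m + (1 − m)pe. With m = 30% in the incentive arms and 10% in the comparison arm, it is 0.65 against 0.55, which is 10 points against the rewarded arms.

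Each rule is right at one extreme. If tests are missed at random, the as-observed share returns 0.50. If only positive tests are missed, counting them as not sober returns 0.50.

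**The case against.** The strongest reply is that the bias needs an analysis the article never states. No section pools morning with evening tests or defines a breath-test endpoint, and that detail may sit in a full protocol or analysis plan that is not shown. This stands: the article does not commit itself to a biased comparison, and the direction of any bias depends on the summary chosen. It does not answer the contradiction between sections, or the fact that the data are collected on unequal schedules.

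A reader might also infer several stronger points that the document does not support.

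- **Skipped tests favor the rewarded arms.** This is a plausible inference from paying more for negative tests, but no section says how a missed test is scored. The wording on larger incentives can be read as giving comparison men smaller ones, which would narrow the asymmetry. Under missed-as-not-sober scoring the bias can reverse.
- **The missing-data rule is wrong for breath tests.** The Analysis section says "we will employ appropriate ad hoc imputation methods to impute missing values" if missingness appears informative. It compares individuals with and without missing data and does not mention missed prompts.
- **The design repeats the displacement seen in the cited incentive study of rickshaw drivers**, where "because drinking at other times increased, overall no reduction in alcohol consumption was observed". That study tested around daytime. This one moves testing to evenings and early mornings, because violence was thought to occur in the evenings. Displacement to other hours remains possible, but the design is not a plain repeat.
- **Sobriety as a whole is not comparable.** Surveys are planned at baseline, immediately after and 3 months after the intervention in every arm, and the baseline survey covers alcohol use. The follow-on criteria do not say that alcohol reduction is judged by breath test. The two incentive arms share one schedule, so their contrast is untouched by frequency and time of day.

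**Conclusion.** The point holds for breath-test results compared between the incentive arms and the comparison arm. The difference in schedule and the contradiction between sections are plain in the text: 12, 14 or 28 comparison tests against 28 or 56 in the incentive arms.

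The size of any distortion is illustrative. The 15 to 20 point figure assumes a pooled positive rate, 50% positive evenings, 10-20% positive mornings and two tests a day in the incentive arms. Other assumed rates give 7.5 to 34 points, and another summary reverses the sign. The effect of missed tests is a conditional caution, not an established bias.

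This should be fixed, but it does not undermine the trial. Feasibility is the main aim, the pilot is unpowered, and the alcohol trend is one of several follow-on criteria. What is at risk is a misleading trend.

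**What to change.** 1. Reconcile the Abstract, Study design, Comparison arm and Incentives arm sections to one stated schedule, giving the number of prompts per man and the time of day for each arm.
2. Base the between-arm breath-test comparison only on evening tests from evenings prompted in every arm. Report morning tests and other-day tests within the incentive arms only.
3. Report missed prompts by arm. Show the result as observed and with missed tests counted as not sober. If men are at least as likely to miss a test after drinking as when sober, the two rules bound each arm's positive share. State that the second can work against the more heavily prompted arms.
4. Call the breath measure evening sobriety, and read it beside the survey measure of alcohol use when judging alcohol reduction.

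The cost is small: mostly wording, with no new data. The extra incentive-arm tests leave the between-arm contrast, and a common prompt calendar is needed so that the shared evenings exist. Step 1 could also change actual prompting, depending on which schedule is in use.

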#### Expected outcomes and results

This pilot study will provide information to determine the design of a future effectiveness trial. Specific outcomes include ability to recruit participants and retain couples across the three arms of the study. We will also assess the effects of intervention on household safety and male partner sobriety, and attitudes and behavior related to gender equality and shared household decision making. Results pertaining to outcomes will be available after the 3 month follow-up following the intervention. The study results will be presented at National and International Research meetings and published in peer reviewed scientific journals. Findings from this pilot study in favor of a follow-on trial will include the following: (1) the intervention is safe and feasible (i.e., no harmful events directly related to the intervention are detected); we are able to recruit participants in a timely manner; loss to follow-up is less than 20% overall and similar in all study arms; and no contamination is detected or if detected, appropriate design changes can be instituted; (2) data on outcomes support the impact of the intervention on alcohol use reduction and couples' communication skills; and trends in alcohol use and IPV incidence are in the direction that supports the positive impact of the intervention; and (3) qualitative evidence similarly supports the feasibility, safety and beneficial impact of the intervention. In conclusion, this study will generate important insights on a novel, urgently needed response to IPV in a high prevalence setting.

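### Breath tests observe sobriety only at the rewarded times of day, while the alcohol go-forward criterion concerns alcohol use in general, so displaced drinking could be read as a reduction

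*Protocol article*

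**What the plan says.** **When men are tested and what is paid.** For the two incentive arms, the Incentives arm section states that "this pilot study incentivized sobriety in the evenings by scheduling daily breathalyzer tests in the evenings and early mornings". Men in these arms are told that "they will receive twice-daily prompts to breathe into their breathalyzer", and the reward is tied to the same tests: "these men will receive larger incentives for negative breathalyzer tests". The comparison arm receives "prompts to men via cell phone messages to breathe into their breathalyzer once every other evening". Study design limits breath testing to four weeks. No daytime test, randomly timed test or unrewarded test is described for the incentive arms.

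**What the protocol knows about displacement.** The Introduction describes a trial of incentives among rickshaw drivers in Chennai. Drinking fell around the test times, but "because drinking at other times increased, overall no reduction in alcohol consumption was observed". Study design takes the length of the incentive period from that trial. Displacement is not mentioned again.

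**What is to be concluded.** Study design hypothesises that incentives will reduce alcohol in the short term. Objectives lists male sobriety among the primary outcomes. Expected outcomes and results makes it a condition favouring a follow-on trial that "data on outcomes support the impact of the intervention on alcohol use reduction". None of these is limited to a time of day. The feasibility analysis plans, if possible, to stratify by how much men drink, judged from their breathalyzer scores.

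**Other alcohol data.** The baseline survey covers alcohol use. Both partners are surveyed again immediately after the intervention and three months later.

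**The concern.** In the incentive arms, the moments at which sobriety is observed are the moments at which it is paid for. A man who moves his drinking out of those hours earns the reward and tests negative, whether or not he drinks less. This is the pattern the Introduction reports from the Chennai trial. The incentive arms have the stronger reason to shift, so the effect would not cancel in a comparison with the control arm.

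Two uses are exposed. One is the go-forward judgement on alcohol use reduction, which could be met on a change of timing alone. The other is the stratification of completion by level of use, which would class men who shifted their drinking as low users. A pilot meant to settle the design of a larger trial should be able to tell less drinking from drinking at other hours.

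**Working it through.** The protocol states no figure for this point, so there is nothing to reproduce. Three checks bear on it.

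**1. Measure against conclusion**

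| Item | Scope in time of day | Section |
|---|---|---|
| Breath tests, incentive arms | evening and early morning, rewarded | Incentives arm |
| Breath tests, comparison arm | alternate evenings | Comparison arm |
| Hypothesis on alcohol | not limited | Study design |
| Go-forward criterion on alcohol | not limited | Expected outcomes and results |
| Stratification by level of use | not limited, but taken from breath scores | Analysis (feasibility) |

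The conclusions are wider than the breath measure. No section names the measure that decides the alcohol criterion.

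**2. How far positive tests can fall with no change in drinking**

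Let p be the share of positive tests before any shift, d the share of evening drinking moved to untested hours, and c the share of moved drinking still detected at a test. With total drinking constant:

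- positive share after the shift = p(1 − d) + p·d·c
- apparent relative reduction = 1 − [p(1 − d) + p·d·c]/p = d(1 − c), whatever the value of p

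Example with p = 50%, d = 50%, c = 25%: 0.50 × 0.50 + 0.50 × 0.50 × 0.25 = 0.3125, and 1 − 0.3125/0.50 = 37.5%.

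| d | c = 0 | c = 25% | c = 50% |
|---|---|---|---|
| 25% | 25% | 18.75% | 12.5% |
| 50% | 50% | 37.5% | 25% |
| 75% | 75% | 56.25% | 37.5% |

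The values of p, d and c are assumptions; the documents give none of them.

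**3. Could moved drinking escape two tests a day?**

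Assume tests at 20:00 and 06:00 and elimination of 0.010 to 0.020 g/dL per hour. Neither is in the documents. The amount cleared is hours × rate, counted from the peak and ignoring absorption.

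- Overnight, peak just after the evening test: 10 h gives 0.10–0.20 g/dL.
- Overnight, peak at 22:00: 8 h gives 0.08–0.16. Peak at midnight: 6 h gives 0.06–0.12.
- Daytime, peak just after the morning test: 14 h gives 0.14–0.28.
- Daytime, peak at noon: 8 h gives 0.08–0.16. Peak at 14:00: 6 h gives 0.06–0.12.

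The two tests bracket the night, so late or heavy night drinking is more likely to be caught in the morning. The daytime gap is the longer one under these times and is the main opening.

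**Side observation on the schedule.** Over 28 days, twice-daily prompts give 2 × 28 = 56 per man and alternate evenings give 28/2 = 14. The Abstract instead has testing "daily for intervention arm participants and three times a week for control participants", which gives 28 and 3 × 4 = 12. These statements need reconciling. A comparison between arms on breath tests should use evening tests matched in timing.

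**The case against.** The strongest reply has four parts.

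- **Alcohol is not measured by breath test alone.** The baseline survey asks about it, and both partners are surveyed twice more. Breath testing is described only for the first four weeks, so the three-month outcome rests on the surveys and interviews. This stands. A reader might infer that sobriety is measured only at rewarded times; that holds for breath tests and not for all alcohol data.
- **No passage says that breath tests decide the go-forward criterion.** The criterion speaks of outcome data in general, adds trends in alcohol use and IPV, and has a qualitative strand. A condensed article may leave the choice of instrument to a fuller document. This also stands, so one may say only that displacement could be read as reduction, not that it would be. What remains is that the one place where the article links level of use to an instrument, the stratification, chooses the breathalyzer.
- **Evening testing is deliberate.** The article expects IPV mostly in the evening, so moving drinking away from that time is partly what the incentive is for. This stands, and the test timing should not be called an error. It supports a claim about evening sobriety, which is narrower than one about alcohol use.
- **The schedule differs from the Chennai trial,** with remote, photo-verified tests twice a day. This narrows the gap, chiefly at night. A reader might also infer fixed clock times known to the men, or that drinking after the evening test would go unseen during the hours of IPV risk. The article gives only times of day, and the morning test may catch such drinking.

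The trial is also a small feasibility study without power for effects. That limits the weight of the point but does not remove it, because the alcohol result is a stated condition for going on.

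**Conclusion.** The concern holds as a mismatch between a stated measure and a stated conclusion. Breath tests in the incentive arms show sobriety in the evening and early morning, when it is rewarded. The hypothesis and the go-forward criterion concern alcohol use in general, and the stratification reads level of use from the breath scores. Given the displacement the article itself reports, a drop in positive tests could be taken for reduced use when drinking has only moved, mainly into the daytime.

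The size cannot be known from the documents. With no true change, the apparent fall is 12.5% to 75% over the assumed range of d and c. How far it would mislead depends on the test times, how much drinking moves, how much of it is still detected, and whether the survey is used to check it.

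The pilot is not invalidated and its evening timing need not change. The conclusion drawn from the breath data should be narrowed and the alcohol criterion anchored to a measure of total consumption.

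**What to change.** 1. Report breath-test results as evening and early-morning sobriety only, and as evening sobriety where the comparison arm is involved.
2. In Expected outcomes and results, require the alcohol use reduction criterion to be supported by total consumption from the male and female surveys already planned.
3. In those surveys, ask about drinking by part of day, with a recall period that covers the four test weeks, so that displacement can be seen. The full questionnaire is not shown and may already do this.
4. Support the stratification by level of use with survey consumption. Baseline consumption has the advantage of being collected before any man can drop out of the intervention.
5. Show breath and survey results side by side by arm, and report any disagreement.

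The cost is a few changes of wording and perhaps one or two survey items. The downside is that survey answers are self-reported by people who know their arm, which is why neither measure should stand alone.

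Optionally, pilot a small number of unrewarded prompts at random times in all arms. This adds burden to as many as 56 prompts per man. Men who have been drinking have little reason to answer, so missed tests are likely to be informative. Response rates should therefore be reported by arm, and these tests should not replace the survey measure.
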